#### Sensitivity Analyses

Sensitivity analyses will be performed to assess the robustness of the results. First, there is likely to be high inter-correlations among all outcomes. We will use multivariate analysis of variance (MANOVA) approach to analyze all outcomes simultaneously. This method accounts for possible correlations among all outcomes and provides for a global assessment of differences between groups with an indication of where differences exist. Second, we will use generalized estimating equations (GEE) [73] to account for possible serial correlation of measurements within a patient overtime. Unlike ordinary linear regression, GEE allows accounting possible correlation of outcome scores for the same patient over time. We will use sensitivity analysis to explore potential clustering of measurements/outcomes from the same patient. The clustering effect, measured by intra-class correlation coefficient, will be assumed to be equal across patients. Sensitivity analysis will also include a between-group comparison of post-intervention comfortable gait speed in participants who completed at least 12 of the 15 training sessions using analysis of variance. Refer to Table 3 for a summary of the planned analyses.

**Table 3 T3:** Summary of planned primary, secondary and sensitivity analyses

*Objective/Variable*	*Hypothesis*	*Outcome measure (type)* *[continuous (c), binary (b)]*	*Method of Analysis*
**1) Primary**			
Walking speed at post-intervention (T2)	MLWP > BWSTT	Comfortable gait speed (c)	ANCOVA
**2) Secondary (T2, T3)**			
Secondary outcomes			
a) Fast walking speed	MLWP > BWSTT	Fast Gait Speed (c)	ANCOVA
b) Walking endurance	MLWP > BWSTT	Six minute walk test(c)	ANCOVA
c) Balance and walking related self-efficacy	MLWP > BWSTT	Activities-specific Balance Confidence Scale (c)	ANCOVA
d) Dynamic balance	MLWP > BWSTT	Functional Balance Test(c)	ANCOVA
e) Mobility participation	MLWP > BWSTT	Life Space Questionnaire (c)	ANCOVA
f) Health-related quality of life	MLWP > BWSTT	Stroke Impact Scale 3.0 (c)	ANCOVA
g) Goal attainment	MLWP > BWSTT	Patient Specific Function Scale(c)	ANCOVA
h) Walking participation	MLWP < BWSTT	Mean daily step activity	ANCOVA
i) Training staff requirement	MLWP < BWSTT	Total number of trainers/number of training sessions (c)	T-test
j) Meaningful change in gait speed of ≥ 0.14 m/s	MLWP > BWSTT	Comfortable gait speed change score T2-T1 ≥ 0.14 m/s)(b)	Chi-square test
Adverse events (count)			
a) Falls during session		Therapist report (b)	Chi-square test
b) Injury during session		Therapist report (b)	Chi-square test
c) Falls between session		Patient report (b)	Chi-square test
d) Myocardial Infarction		Patient report/health record (b)	Chi-square test
e) New stroke		Patient report/health record (b)	Chi-square test
f) Hospitalization		Patient report/health record (b)	Chi-square test
g) Death (all causes)		Health record/Physician (b)	Chi-square test

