## Methods/design

### Design Outline

This study is a prospective, randomized, single blind, balanced parallel-group (1:1) superiority trial with stratification by baseline comfortable gait speed (< 0.5 m/s and ≥ 0.5 m/s). The design includes concealed allocation during recruitment and screening, blinded outcome assessment and intention to treat analysis. Refer to Figure 1 for study design diagram.

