### Randomization

Participants will be randomly allocated to the two active intervention groups using a fixed allocation ratio of 1:1. Consistent with previous studies in this area [19,33], we anticipate the response to both training programs to be associated with pre-treatment walking ability and participants will be stratified by baseline comfortable gait speed (slow < 0.5 m/s and fast ≥ 0.5 m/) to minimize group imbalances on this variable [37]. In order to maintain recruitment balance between groups throughout the trial, a permuted block randomization process will be used within each strata using block sizes of at least 2 with all blocks divisible by 2 [38]. The randomization creation process (including block sizes) and resulting schedule will be set, held and managed by a central randomization service (Biostatistics Unit at St. Joseph's Healthcare Hamilton). Group assignment will be communicated by email to the research coordinator on a single participant basis after screening, written informed consent, and baseline assessments have been completed.

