### Statistical Analysis

The trial results will be reported in accordance with the CONSORT criteria [http://www.consort-statement.org]. The flow of patients in the trial will be summarized using a flow-diagram. The baseline characteristics and outcomes scores of the patients will be analyzed using descriptive statistics reported by group as mean (standard deviation [SD]) or median (first quartile [Q1], third quartile [Q3]) for continuous variables depending on the distribution and count (percent) for categorical variables. Intention to treat analysis technique will be used for the primary analysis [71]. Missing data will be handled through multiple imputation technique [72]. All statistical tests will be performed using two-sided tests at the 0.05 level of significance. The Tukey's HSD method will be used to adjust the level of significance for testing for secondary outcomes. For all models, the results will be expressed as estimate of mean difference (or odds ratios for binary outcomes), standard errors, corresponding two-sided 95% confidence intervals and associated p-values. P-values will be reported to three decimal places with values less than 0.001 reported as < 0.001. Adjusted analyses will be performed using regression techniques to investigate the residual impact of key baseline characteristics on the outcomes (i.e. age, time since stroke onset, comfortable gait speed, and training site). Goodness-of-fit will be assessed by examining the residuals for model assumptions and chi-squared test of goodness-of-fit. All analyses will be performed using SPSS version 16.0 for Windows or SAS 9.2 (Cary, NC).

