#### Primary Analysis

The post-intervention (T2) self-selected overground walking speed for the MLWP and BWSTT groups will be compared using analysis of covariance. The two factors will be intervention group (intervention or control) and baseline speed stratum (i.e. slow or fast).

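### The responder comparison (gain of at least 0.14 m/s) uses a chi-square test that ignores the baseline-speed stratum: valid, but conservative and less efficient to the extent that the stratum predicts response

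*Protocol article*

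**What the plan says.** - **Outcome and test.** Table 3, secondary row j, defines response by "Comfortable gait speed change score T2-T1 ≥ 0.14 m/s)(b" and names "Chi-square test" as the method, with no stratum or covariate. The hypothesis is that MLWP does better.
- **Design.** The Design Outline specifies "stratification by baseline comfortable gait speed (< 0.5 m/s and ≥ 0.5 m/s". The Randomization section gives the reason: "we anticipate the response to both training programs to be associated with pre-treatment walking ability".
- **Primary model.** For post-intervention comfortable gait speed, the Primary Analysis section states: "The two factors will be intervention group (intervention or control) and baseline speed stratum (i.e. slow or fast". Table 3 also gives ANCOVA for secondary rows a to h.
- **Reporting.** The Statistical Analysis section says that, for all models, "results will be expressed as estimate of mean difference (or odds ratios for binary outcomes), standard errors, corresponding two-sided 95% confidence intervals" and p-values will be given.
- **Adjusted analyses.** The same section adds: "Adjusted analyses will be performed using regression techniques to investigate the residual impact of key baseline characteristics on the outcomes". Comfortable gait speed is among the characteristics listed.

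**The concern.** The same measurement, comfortable gait speed, is analysed with the stratum in the primary model and without it in row j. Stratified allocation balances the arms on baseline speed. If speed also predicts response, the true variance of the between-arm difference is smaller than the variance an unstratified test assumes. The test then rejects less often than 5% under the null hypothesis and has less power than the data allow. Row j is the only binary efficacy outcome in Table 3 and is labelled as meaningful change. Dichotomizing has already cost it power, so a further avoidable loss is worth removing. An odds ratio taken from the unstratified table would also ignore the stratum.

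**Working it through.** **1. The plan's own figures.** Inputs from the Sample size section: difference 0.14 m/s, SD 0.19 m/s, two-sided 5%, power 80%, loss 17%.

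n = 2 × (1.96 + 0.842)² × 0.19² / 0.14² = 28.9, so 29 per arm. 29 / (1 − 0.17) = 34.9, so 35 per arm. Both agree with the article and supply the arm sizes used below.

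**2. Why the unstratified test is conservative.** Let stratum s hold a share w_s of each arm and have response p_s, with p̄ = Σ w_s p_s. The chi-square test uses p̄(1 − p̄). With arms balanced within strata, the relevant quantity is Σ w_s p_s(1 − p_s), which is smaller by Σ w_s(p_s − p̄)². If R is the ratio of the second to the first, the effective critical value is 1.96/√R.

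The article gives neither response rates nor stratum sizes. Assumed here: 15 slow and 14 fast participants per arm.

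| Response slow / fast | p̄(1 − p̄) | Σ w_s p_s(1 − p_s) | R | 1.96/√R | Approx. type I error |
|---|---|---|---|---|---|
| 30% / 50% | 0.2393 | 0.2293 | 0.958 | 2.00 | 4.5% |
| 20% / 60% | 0.2386 | 0.1986 | 0.832 | 2.15 | 3.2% |
| 15% / 65% | 0.2382 | 0.1758 | 0.738 | 2.28 | 2.2% |

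**3. Simulation of both tests.** Pearson chi-square against Mantel-Haenszel, no continuity correction, 29 per arm, treatment odds ratio 4 within each stratum (assumed) for power. Repeat runs agree to within about one point.

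| Control response slow / fast | Type I error, unstratified v stratified | Power, unstratified v stratified | Loss |
|---|---|---|---|
| 30% / 50% | 4.1% v 4.6% | 69% v 70% | about 1 point |
| 20% / 60% | 2.8% v 4.9% | 58% v 65% | about 7 points |
| 15% / 65% | 2.0% v 5.1% | 46% v 59% | about 13 points |

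The simulated type I errors lie a little below those in step 2 because the counts are small and discrete.

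**4. A second set of assumptions, tied to the plan's SD.** Normal change scores with SD 0.19 m/s, BWSTT mean change 0.07 m/s (assumed), treatment difference 0.14 m/s, and a varying gap between strata in mean change:

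| Gap (m/s) | Power at 29 per arm, unstratified v stratified | Power at 35 per arm, unstratified v stratified |
|---|---|---|
| 0 | 59.6% v 59.7% | 65.9% v 66.0% |
| 0.10 | 56.7% v 57.9% | 63.1% v 65.7% |
| 0.15 | 53.4% v 56.6% | 58.9% v 65.1% |
| 0.20 | 48.0% v 54.9% | 54.4% v 63.9% |

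At a gap of 0.20 m/s the unstratified type I error is 3.0% (29 per arm) and 3.4% (35 per arm).

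**5. How large a stratum effect step 3 assumes.** On the same normal scale the gap is 0.19 × (z_fast − z_slow), where z is the normal quantile of the response rate:
- 30% / 50%: 0.19 × (0 + 0.524) = 0.10 m/s
- 20% / 60%: 0.19 × (0.253 + 0.842) = 0.21 m/s
- 15% / 65%: 0.19 × (0.385 + 1.036) = 0.27 m/s

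**6. Can a 2×2 table give the promised estimate?** Illustrative counts 20/35 v 12/35: odds ratio = (20 × 23)/(15 × 12) = 2.56. SE of the log odds ratio = √(1/20 + 1/15 + 1/12 + 1/23) = 0.493. The 95% CI is 0.97 to 6.72. It can.

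**The case against.** **The size is assumed.** The article expects an association but does not quantify it. The two scenarios with a clear loss need strata differing in mean change by 0.21 and 0.27 m/s, which is 1.5 and 1.9 times the 0.14 m/s treatment effect. The outcome is a change from baseline, so a strong link between stratum and speed need not mean an equally strong link with change. This stands: the loss must be stated as conditional, and it may be about a point or less.

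**Dichotomizing costs more.** At 29 per arm the primary comparison has 80% power, while the responder comparison has about 60% even with no stratum effect. This also stands, and stratifying does not recover that part.

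**Adjusted regressions are already planned.** They are, and they list comfortable gait speed. But their stated purpose is to examine the residual influence of baseline characteristics. They do not replace the test that Table 3 assigns to row j, so this objection does not remove the point.

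**Stronger readings.** A reader might infer that a chi-square analysis cannot yield an odds ratio and confidence interval. Step 6 shows that it can, and the Statistical Analysis section commits to "or odds ratios for binary outcomes), standard errors, corresponding two-sided 95% confidence intervals", so there is no ground to expect a bare p-value. A reader might also infer that the analysis cannot be combined with the planned multiple imputation. A log odds ratio from each imputed table can be pooled, and pooling mechanics belong in the analysis plan, which is not shown.

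**Conclusion.** The point holds as an efficiency issue in one secondary outcome. Row j omits a stratum that was used to randomize, is expected to be prognostic, and is in the primary model. The cost at 29 per arm runs from essentially nothing to about 13 points of power, depending on assumed response rates, stratum sizes and odds ratio, none of which the article gives. On the scale of the plan's own SD it is about 1 point at a 0.10 m/s gap and 7 points at 0.20 m/s; at 35 per arm the latter is about 9 points.

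This is not a validity problem, because the error is on the conservative side. In the scenarios examined the stratified test was no less powerful, so adjusting costs nothing even if the stratum proves weak. The primary analysis and the sample size of 70 are untouched.

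**What to change.** In Table 3, row j, replace the chi-square test with logistic regression of response on treatment and baseline speed stratum, or with a Mantel-Haenszel test and common odds ratio stratified by it. Report the stratum-adjusted odds ratio with its 95% confidence interval, as the Statistical Analysis section already promises, together with the response percentage in each arm. Say that this odds ratio is conditional on stratum, since it will generally differ from the one in the unstratified table.

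Cost: one line in Table 3 or the analysis plan. No new data are needed, because the stratum is recorded at randomization.

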**3) Sensitivity Analysis**			
a) All outcomes analysed simultaneously to account for correlation among them		Primary and secondary outcomes	MANOVA
b) Serial correlation of all outcomes at baseline, T2, T3		Primary and secondary outcomes	GEE
c) Completers (≥ 12 sessions)	MLWP > BWSTT	Comfortable Gait speed	ANCOVA

IMPORTANT REMARKS:

The GEE^2 ^is a technique that allows to specify the correlation structure between patients within a hospital and this approach produces unbiased estimates under the assumption that missing observations will be missing at random. An amended approach of weighted GEE will be employed if missingness is found not to be at random^3^.

In all analyses results will be expressed as coefficient, standard errors, corresponding 95% and associated p-values. Goodness-of-fit will be assessed by examining the residuals for model assumptions and chi-squared test of goodness-of-fit

Tukey's HSD method will be used to adjust the overall level of significance for multiple secondary outcomes

^2^Hardin JW. *Generalized Estimating Equations*. New York: Chapman and Hall/CRC, 2001

^3 ^Diggle PJ, Liang K-Y, Zeger S. *Analysis of Longitudinal Data*. Oxford: Oxford Science Publications, 1994.

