### Sample size

Seventy participants will be recruited. The sample size has been calculated to reliably detect a 0.14 m/s between-group difference in gait speed change (assuming a standard deviation of 0.19 m/s) with 80% power at a 2-tail significance level of 0.05. Using self-selected gait speed as the primary outcome, this sample size has been estimated based on a range of change scores and standard deviation values reported in the literature. Reported differences in change scores between experimental and control interventions range from 0.9 m/s to 0.14 m/s and standard deviation in change scores range from 0.14 to 0.19 m/s [19,33,34,69,70]. Using a conservative estimate of standard deviation of change score of 0.19 and a difference between group change scores of 0.14 m/s, the minimal number of participants required for each treatment group is 29 participants. Dropout rates in previous studies have ranged from 7 to 20% [19,33]. Allowing for a 17% loss to follow up rate, the study will need to recruit approximately 35 participants into each group for a total of 70.

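### The Table 3 remark on the GEE sensitivity analysis misstates when plain and weighted GEE are valid with missing data, and its hospital-level correlation conflicts with the within-patient analysis planned elsewhere

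*Protocol article*

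**What the plan says.** The Sensitivity Analyses section introduces GEE "to account for possible serial correlation of measurements within a patient overtime". It adds that the clustering of interest is among scores from one patient, with an intra-class correlation taken as equal across patients. Table 3 row 3b agrees: serial correlation of the primary and secondary outcomes over baseline, T2 and T3.

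The remarks under Table 3 differ. For the correlation, they describe GEE by what it can do: it "allows to specify the correlation structure between patients within a hospital". For missing data, their claim about GEE reads: "this approach produces unbiased estimates under the assumption that missing observations will be missing at random". The next sentence sets the fallback: "An amended approach of weighted GEE will be employed if missingness is found not to be at random".

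The Statistical Analysis section says, without limiting it to one analysis, that missing data will be multiply imputed. The Sample size section allows for 17% loss to follow-up and cites 7 to 20% in previous studies.

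**The concern.** Two things in the remark look wrong.

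The first is the pairing of method and assumption. An analyst who follows the remark keeps unweighted GEE under MAR, where it is not generally unbiased. The same analyst turns to weighted GEE under MNAR, where weights built from observed history do not remove the bias. The move between them depends on a finding that observed data cannot deliver, because MAR and MNAR differ only in how missingness depends on values nobody saw.

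The second is the unit of clustering. Patient and hospital are different clusters and give different standard errors, and the article names both for one analysis.

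At stake is how a sensitivity analysis covering all outcomes is run and described. With 17% loss allowed for, missing data are expected, and a report could call its GEE estimates unbiased on an assumption that does not secure that.

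**Working it through.** **The plan's own figure.** The GEE remark carries no number. The Sample size section supplies the effect and SD used below, and its result reproduces. Inputs: difference 0.14 m/s, SD of change 0.19 m/s, 80% power, two-sided 0.05, allocation 1:1.

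- n per group = 2 × [0.19 × (1.960 + 0.842) / 0.14]² = 28.91, so 29, as stated.
- 29 / (1 − 0.17) = 34.9, so 35 per group and 70 in total, as stated.

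Nothing in this point changes these figures.

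**Missing-data rule, side by side.**

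| Mechanism | Method under the remark | General property |
|---|---|---|
| MCAR | unweighted GEE | valid |
| MAR | unweighted GEE | not valid in general; weighted GEE, or GEE on properly imputed data, is |
| MNAR | weighted GEE | still biased |

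**Simulation to check the ordering.** There were 400,000 patients per scenario, three visits, and a true group difference of 0.14 m/s at T2 and T3. These assumptions are not in the documents:

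- Level SD 0.25 m/s and correlation 0.711, chosen because 0.25 × √[2 × (1 − 0.711)] = 0.19, the plan's SD of change.
- Monotone dropout of about 15 to 18% by T3.
- In the MAR and MNAR scenarios, strong dependence of dropout on speed, in opposite directions in the two arms. This is a deliberately adverse pattern.

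Estimated difference, T2 / T3 (truth 0.140):

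| True correlation, mechanism | Unweighted, independence | Unweighted, exchangeable | Weighted |
|---|---|---|---|
| Exchangeable, MCAR | 0.140 / 0.141 | 0.140 / 0.141 | 0.140 / 0.141 |
| Exchangeable, MAR | 0.189 / 0.219 | 0.144 / 0.146 | 0.140 / 0.140 |
| Exchangeable, MNAR | 0.192 / 0.221 | 0.167 / 0.173 | 0.167 / 0.174 |
| AR(1), MAR | 0.189 / 0.204 | 0.149 / 0.138 | 0.139 / 0.138 |
| AR(1), MNAR | 0.191 / 0.221 | 0.169 / 0.180 | 0.166 / 0.185 |

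Under MAR, unweighted GEE is off by +0.049 / +0.079 m/s with independence and true exchangeable correlation. With an exchangeable working structure it is off by +0.004 / +0.006 if that structure is right, and by at most 0.009 if it is wrong. Weighting brings the MAR bias to within about 0.002. Under MNAR the weighted estimate remains off by +0.026 to +0.045.

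**Less adverse dropout.** With about 15% lost after T2 only, depending on T2 speed:

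- Exchangeable working and true correlation (0.711 or 0.9): T3 estimate 0.140 to 0.141, even with arm-opposed dropout.
- Non-exchangeable truth (0.711 with baseline, 0.9 between T2 and T3), exchangeable working structure: 0.137 with the same dropout slope in both arms, 0.150 with opposed slopes.
- Independence with the same slope in both arms: 0.128 to 0.131, a bias of about −0.01.

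**Cluster unit.** The Participants section names three hospitals. A group-by-visit model has 2 × 3 = 6 coefficients. The middle term of the robust variance is a sum of one outer product per cluster, so with three clusters its rank is at most 3. It cannot support six coefficients.

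**The case against.** The best defence is terminological. If the authors meant completely at random where they wrote at random, both sentences about missing data become correct. That may well be the intention. But MAR is a defined term and the text as printed tells the analyst the wrong thing, so it needs correcting on either reading.

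A reader might infer that the GEE analysis cannot do its job as a robustness check. The documents do not support that. The job given to it is to allow for serial correlation within a patient, and the Sensitivity Analyses text and row 3b define that consistently. The hospital phrase occurs once, in a general description of the technique. No hospital-level analysis is laid out, and training site enters as a covariate in the adjusted analyses. The three-cluster problem would therefore arise only if someone acted on that phrase.

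A reader might also infer a sizeable bias in this trial. That does not follow. The document says nothing about dropout depending on walking speed. The allowance is 17%, and 20% is only the top of the range cited from other studies. The equal intra-class correlation suggests an exchangeable structure, though the text does not name one, and under it the bias is small.

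Finally, multiple imputation is planned in general terms. If it feeds the GEE, the analysis is valid under MAR, given a sound imputation model, without weights. How the two fit together is a detail an article may leave to fuller documents. This limits the harm but does not make the remark right.

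**Conclusion.** The remark is wrong as written, in a limited way. Unweighted GEE is not generally unbiased under MAR, weighted GEE does not repair MNAR, and the condition for switching cannot be established from observed data. The hospital wording contradicts the within-patient clustering stated elsewhere, and with three hospitals it would not give usable robust standard errors.

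The likely size is modest: about 0 to 0.01 m/s under MAR with the implied exchangeable structure, against a target difference of 0.14 m/s. The values of +0.05 to +0.08 m/s need an independence structure and arm-opposed dropout together. All of these rest on assumed dropout and an assumed level SD. They show direction and dependence, and do not forecast this trial's bias. The fault lies in a sensitivity analysis; the primary ANCOVA and the sample size are unaffected.

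**What to change.** - State that the cluster is the patient, name the working correlation, and delete the phrase about patients within a hospital.
- Drop the claim that unweighted GEE is unbiased under MAR. For MAR, run the GEE on the multiply imputed data already planned in the Statistical Analysis section, or use weighted GEE, and say which.
- Replace the trigger based on finding that data are not missing at random with a pre-planned MNAR sensitivity analysis, for example delta-adjusted imputation over a stated range.

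The cost is a few sentences and one extra sensitivity run. No new data are needed, and the sample size and primary analysis stay as they are.
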